| --- |

| **METHODS**  [Study design] A randomized, double-blind, placebo-controlled parallel clinical trial.  Randomization,  n=60  COPD  Study group, n=40  Week 0  Week 4  Week 8  Week 12  Control group, n=20  [Inclusion criteria] We will enroll 60 subjects with:   1. moderate-to-severe COPD patients 2. aged 40-79 years, 3. abstaining from cigarette smoking or maintaining a stable dose of cigarette consumption, 4. no acute exacerbation of COPD, 5. clinically being stable for one month and longer, 6. not undergoing exercise training program.   [Exclusion criteria] Patients should have no   1. uncontrolled diabetes mellitus by plasma fasting sugar >200 mg/dl, 2. uremia or CKD stage 5, 3. chronic heart failureby NYFC III, 4. cerebrovascular disease, 5. uncontrolled anemia by Hb < 10 mg/dl, 6. active malignant diseases, 7. other hospitalized acute illness, 8. systemic prednisolone > 10 mg per day.   [Randomisation] All legible subjects with moderate-to-severe COPD will be enrolled after signing the informed consent. All subjects will undergo the first set of measurements as follows. All subjects will be allocated in random order, double-blind, and placebo-control. The study group will contain 40 subjects taking Rhodiola L extract capsule Rhodiola L 250mg twice per day for 12 weeks and the control group will contain 20 subjects taking the placebo of the same dose for the same period of time. The placebo medication appears the identical figure and odor to the Rhodiola L extract capsule and is delivered by a pharmacist who is naïve to the measurement items and outcomes. The side effects and serious adverse effects of Rhodiola L extract capsule will be reported every time they occur by the patient and inquired monthly by the study nurse. Twelve weeks later, all subjects will undergo the second set of measurements. Each subject will revisit the out-patient clinic every month, totally four visits for each subject.  [Outcome measurements]  Primary endpoint: six-minute walk distance in meters at week 12.  Seconadary endpoins  (1) Demographics: age, body weight and height, gender measured by a study nurse  (2) Anthropometrics: mid-arm circumference and triceps skin thickness measured by a dietitian. See below.  (3) Symptomatology: dyspnea index: visual analog scale (VAS), exertional dyspnea: Borg scale12 and the modified Medical Research Council (mMRC)13, oxygen-cost diagram (OCD)14, cough: COPD assessment test (CAT) score, sputum: amount and color, evaluated by a study nurse  (4) Composite index: BODE15, the sum of B: BMI=body mass index, O: obstruction shown by FEV1%pred, D: dyspnea shown by themMRC.(5) Quality of life: Chronic respiratory disease questionnaire16 (CRDQ), St. George Respiratory disease questionnaire17 (SGRQ), hospital anxiety and depression scale18 (HADS), sleep quality: Epword Sleepiness scale, sex: International Index of Erectile Function (IIEF-5) evaluated by a study nurse.  (6) Lung function and 6-minute walk test (6MWT): spirometry, lung subdivisions, diffusing capacity for carbon monoxide, maximum inspiratory/expiratory pressure performed by a technician at the lung function lab of Da-Ching (大慶) Main Hospital. Protocol: see below. 6MWT19 will performed by the study nurse. Protocol: see below.  (7) Cardiopulmonary exercise test20 and 75% peak-work-rate constant work-rate exercise.21 All exercise tests will be performed by a technician at Zhong Xing (中興) Branch. Protocol: see below.  (8) Episodes of COPD acute exacerbations: recorded by a study nurse. Definition of acute exacerbation: more cough with more yellow sputum than usual or need more prednisolone for rescue or need antibiotics for possible infection or more dyspneic which makes the subject to visit the ER or to be hospitalized.  (9) Biomarkers: IL-1, TNF-, CRP, MMP-9.1, IL-4, and IFN-γ.  [Procedures]  *Anthropometric measurements.* Triceps skinfold thickness is measured with calipers, while the mid-upper arm circumference is measured with a tapeline. Both measurements are taken midway between the tip of the olecranon process and the acromion process, in the midline of the posterior surface of the extended dominant arm. All measurements are made thrice by an expericenced nutritionist and the middle value is recorded for analysis.  *Lung function test protocol.* Pulmonary function tests are performed before exercise testing to identify moderate-to-severe COPD. FEV1 is measured with a mass flow sensor spirometer (Yorba Linda, CA, USA) at body temperature, ambient atmospheric pressure, and fully saturated (BTPS). The best of three technically satisfactory readings is used. The total lung capacity (TLC), residual volume (RV), and carbon monoxide diffusing capacity (DLCO) are also measured (Yorba Linda, CA, USA). All the lung function data are obtained after inhaling 400 g of fenoterol HCl. DLCO is measured by the single-breath technique. Simple volume calibration is conducted with a 3-L syringe before each test. For the predicted race-adjusted values of FEV1, forced vital capacity (FVC), TLC, and DLCO used by the institution, please refer to selected reference.[19,22-24](#_ENREF_13) Maximum inspiratory pressure (MIP) at the mouth is measured at RV with a forceful inspiratory maneuver leading to a sustained maximal effort followed by natural release upon fatigue (Yorba Linda, CA, USA). Maximum expiratory pressure (MEP) is measured at TLC. MIP and MEP are both performed on three occasions with a 1-minute recovery period between efforts. The best result is recorded for analysis. For determining breathing reserve, the direct maximum voluntary ventilation (MVV) is calculated from a 12-second maneuver of rapid and deep breathing as recommended for COPD patients [25](#_ENREF_17).  *Six-minute walk test protocol*. The walk tests are conducted in a temperature-controlled corridor. Before and immediately after the walk test, systemic arterial blood pressure and respiratory frequency are measured. The perceived exertion is measured with a modified Borg score at rest, midway through and at the end of the walk. Patients are instructed to walk as far as possible with the help of verbal encouragement by an experienced investigator, as Guyatt et al.26 recom-mended. Patients are allowed to stop to rest if needed. Oxyhaemoglobin saturation determined by pulse oximetry (SPO2) (Ohmeda 3760) and the heart rate readings are stored and later printed out as 15-sec averages. The absolute change in the heart rate in response to walk test is the difference between the baseline and the end. The change in SPO2 is the absolute change from the baseline to the nadir during the walk. Each patient performs two to three repetitions of walk tests separated by 2±4 h of rest. The highest distance walked in the 6 min (D) is recorded in meters. The distance is then converted to DW by multiplying by the body weight in kilograms.19  *Cardiopulmonary exercise test protocol.* After acclimating to the computer-controlled and electronic-braked cycle ergometer (Yorba Linda, CA, USA) and a 2-minute rest period, each patient began a 2-minute period of unloaded cycling followed by a ramp-pattern exercise test to the limit of their tolerance. Work rate is selected at a slope of 5 to 20 watts per minute according to pre-determined fitness based on our derived protocol formula.[14](#_ENREF_18)  Twelve-lead electrocardiography, heart rate, oxyhemoglobin saturation (SPO2), O2 (ml/min), CO2 (ml/min), minute ventilation (E), blood pressure, and Borg score were measured. Heart rate and SpO2 using a pulse oximeter (Ohmeda 3740, BOC Health Care Company, CO, U.S.A.) were measured continuously. Borg score was used to rate the perceived dyspnea from a scale of 0 to 10 during the course of exercise testing following appropriate instruction before exercise testing.[12](#_ENREF_19) Calibrations of the preVentTM pneumotachograph were performed with a 3-L syringe before each test. The O2 and CO2 analysers were calibrated with standard gases. The anaerobic threshold was determined using dual method approach [20](#_ENREF_1) containing modified V-slope method [27](#_ENREF_20) and the ventilatory equivalents methods. [28](#_ENREF_9)  The study will cover the expenditure of hospitalization that the adverse events related, although the advert events should be extremely low. The study will offer a 24-h a day service if the participants have any adverse events to report. All the study materials will be preserved safely at our study site.  **Biochemical diagnosis**  Measurement of routine blood indices, including alanine transaminase (ALT), aspartate aminotransferase (AST), creatinine, and blood urea nitrogen (BUN) detection (Automatic analyzer, ARCO, Biotechnica Instruments, Italy) will be processed at the indicated time.  **Cytokine determination**  Cytokine determination by ELISA according to the manufacturer’s instructions (Pharmingen, San Diego, CA, USA). Cytokines (IL-1, TNF-, CRP, MMP-9, IL-4, and IFN-γ) were assayed in triplicate using commercial ELISA kits as described elsewhere (Tsai et al., 2000; Lin et al., 2004; Ho et al., 2005; Huang et al., 2005; Lin et al, 2005a, 2005b, Lin et al., 2006). Using 96-well plates, 100 μl anti-mouse capture antibody diluted 1:250 was added and incubated overnight at 25°C. Serum samples or the standard were added (100 l/well), and plates were incubated at 25°C for 2 h. After incubation, plates were washed five times with ELISA washing solution, and 100 μl biotinylated anti-mouse monoclonal antibody conjugated to horseradish peroxidase, diluted 1:250 in assay diluents, was added to each well. Plates were incubated at room temperature for 1 h. After incubation, the wells were washed seven additional times with ELISA washing solution using an ELISA washer (Bio-Rad, Hercules, CA, USA). Substrate solution (tetramethylbenzidine, 100 l) was added, and the plates were incubated at 37°C for 15 min. The reaction was then terminated by the stop solution (2N H2SO4), and absorbance was read at 450 nm with a spectrophotometer (Model 550, Bio-Rad). For every test, a standard curve was also derived for IL-4 and IFN-γ. The range of the standard curve extended from and 15.6 pg–8000 pg for IFN-γ.  試驗品部分(劑量與用法)：  試驗物質類別型態： 紅景天濃縮細粒  衛署藥製第055161號  主要成分：   | 處方成分 | | | | --- | --- | --- | | 成分內容 | 成分數量 | 成分單位 | | 紅景天 | 1.5 | g | | 以上生藥製成浸膏0.45g(生藥與浸膏比例1.5：0.45＝3.3：1) |  |  | | 微結晶纖維素 | 0.35 | g | | starch | 0.2 | g |   包裝方式：4~1000公克塑膠瓶裝  規格與濃度：500mg/顆  儲存溫度：室溫陰涼通風處  用量用法：紅景天組:成人每日1次、每次1顆 (與食物錯開至少半小時，配溫開水服用)    Statistical analysis：  The intent-to-treat analysis was used in the study. Data were summarized as mean  standard deviation (SD) or median (interquartile). A linear mixed model was used to compare the means in each variable between pre- and post- interventions and to test these pre-post differences between the study and the placebo groups. For each variable, the comparisons were planned priori and were simultaneously performed by setting up appropriate dummy variables and interactions with random effects in linear mixed models. For non-normal data, the Mann-Whitney test was used. The chi-square test or Fisher exact test was used to compare the proportion of the categorical variables between the two groups. A *p* value of less than .05 was considered to be statistically significant, and a *p* value of less than .1 but more than .05 was considered to have a trend. Statistical procedures were performed using the SAS software package version 9.3 (SAS Institute Inc., Cary, NC) and Microcal Origin v 4.0 (Northampton, MA, USA).  We estimated that there was a statistical power of 0.8 for 6MWD, given the 6MWD in the study from 456 meters to 482 meters in the study group and no improvement in the control group, the sample size is 60 subjects including an expected 20% dropout rate.   |  | | | | | | | --- | --- | --- | --- | --- | --- | | week  variables | week 0 | week 4 | week 8 | week 12 | note | | (1)physical examination |  |  |  |  |  | | (2)CRDQ |  |  |  |  |  | | (3)SGRQ |  |  |  |  |  | | (4)HADS |  |  |  |  |  | | (5)BDI |  |  |  |  |  | | (6)TDI |  |  |  |  |  | | (7) adverse effects |  |  |  |  |  | | (8)CRE |  |  |  |  |  | | (9)CBC |  |  |  |  |  | | (10)GPT |  |  |  |  |  | | (11)lung function |  |  |  |  |  | | (12)cardiopulmonary exercise test |  |  |  |  |  | | (13)6MWT |  |  |  |  |  | | (14) IL-1 |  |  |  |  |  | | (15)TNFα |  |  |  |  |  | | (16)HS-CRP |  |  |  |  |  | | (17)MMP9 |  |  |  |  |  | |

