**Abstract**

| **（Keyword :** *COPD, Rhodiola L., clinical trial, biomarkers, spirometry, exercise testing, quality of life***）**  **BACKGROUNDS.** Chronic obstructive pulmonary disease (COPD) has been one of the top ten causes of death in our Taiwanese population. Most patients present dyspnea and exercise intolerance because of the deranged lungs and impaired skeletomuscular function. Recently, low-grade systemic inflammation plays a vital role in its pathogenesis. Despite the mainstay of treatment using the inhaled medications that may lead to slowdown the progression of impaired lung function, improve the quality of life, and reduce the episodes of acute exacerbation, in turn the systemic inflammation is on-going and is hardly controlled by local therapy.  Herb medicine like Rhodiola L extract capsule contains p-tryosol, salidroside, rosavin, pyridrde, rhodiosin and rhodionin and has its anti-inflammatory and anti-oxidative effects and minimum side-effect after a long-term use as reported in the literature.    **AIMS.** We hypothesize that add-on Rhodiola L extract capsule to the regimen of patients with moderate-to-severe COPD (1) may provide a potential of systemic effects of anti-inflammation and anti-oxidation for these patients, and these effects (2) may reflect in the improvement of patients’ physiological measurements, quality of life and exercise tolerance.  **METHODS**  [Study design] A randomized, double-blind, placebo-controlled clinical trial.  [Subjects] We will enroll 60 moderate-to-severe COPD patients aged 40-79 years, abstaining from cigarette smoking or maintaining a stable dose of cigarette consumption, no acute exacerbation of COPD, being stable for one month and longer, or not undergoing exercise training program. Patients should have no uncontrolled diabetes mellitus, uremia, chronic heart failure, cerebrovascular disease, uncontrolled anemia, late-stage malignant diseases, or other acute illness, or taking any systemic anti-inflammatory agents.  [Procedures and Randomisation] All elegible subjects with moderate-to-severe COPD will be enrolled after signing the informed consent. All subjects will undergo the first set of measurements as follows. All subjects will be allocated as the study designed. The study group will contain 40 subjects taking Rhodiola L extract capsule Rhodiola L 250 mg twice per day for 12 weeks and the control group will contain 20 subjects taking the placebo of the same dose for the same duration.  [Measurements Set] (1) demographics, (2) anthropometrics, (3) symptomatology: dyspnea index, cough, sputum, sleep, sex, (4) composite index: BODE, (5) quality of life, (6) lung function, 6MWT and exercise test, (7) COPD acute exacerbations, and (8) biomarkers: IL-1, TNF-, CRP, MMP-9, IL-4, and IFN-γ.  [Primary endpoint] Difference of 6 minutes walking distance at week 12. |

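### The only haemoglobin threshold in the protocol is given in mg/dl, so the number in the anaemia exclusion cannot exclude anyone as written

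*Protocol*

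**What the plan says.** The anaemia exclusion appears twice in the protocol.

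- **Abstract, [Subjects].** Uncontrolled anaemia is one of a list of conditions that bar entry: "Patients should have no uncontrolled diabetes mellitus, uremia, chronic heart failure, cerebrovascular disease, uncontrolled anemia, late-stage malignant diseases". No number or unit is attached.
- **METHODS, [Exclusion criteria], item 5.** The same condition is given a numeric limit: "uncontrolled anemia by Hb < 10 mg/dl".

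Item 1 of the METHODS list also uses mg/dl, there for glucose: "uncontrolled diabetes mellitus by plasma fasting sugar >200 mg/dl".

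The primary endpoint is a walking test: "Primary endpoint: six-minute walk distance in meters at week 12". Secondary measurements include single-breath diffusing capacity, a ramp cycle test taken to the patient's limit, and a constant work-rate test at 75% of peak. A blood count (CBC) is a row in the visit table, but the visit marks cannot be read in the text at hand, so its timing is unknown to us.

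**The concern.** Haemoglobin concentration is ordinarily reported in grams per decilitre, or grams per litre. A limit of 10 in milligrams per decilitre lies far below any value a laboratory could return for a patient. The criterion therefore reads as a working threshold but cannot be met.

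This matters because item 5 is the only operational definition of an exclusion that the protocol says it applies. Haemoglobin affects oxygen delivery and measured diffusing capacity, so it bears on the walking distance, the cycle tests and DLCO. The analysis is by intention to treat, so a patient admitted against the protocol's intent would stay in the comparison. Eligibility and protocol deviations are also judged against the written text. By the number, a patient with severe anaemia passes; by the words, the same patient does not. Study nurses do the screening, and they need a limit that they can apply as it stands.

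**Working it through.** The protocol derives no figure here, so there is no calculation of its own to reproduce. The check is a unit conversion and a search for any other statement of the threshold.

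**Inputs**

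- Cut-off: 10 mg/dl (METHODS, exclusion item 5).
- Abstract: uncontrolled anaemia, with no number.
- Range of haemoglobin in patients: not given in the protocol. Assumed here to be 3 to 20 g/dl, deliberately wide.

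**Step 1: convert the cut-off.** 1 g = 1,000 mg, so 10 mg/dl ÷ 1,000 = 0.01 g/dl, which is 0.1 g/L.

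**Step 2: apply it literally.** A patient is excluded if haemoglobin in mg/dl is below 10.

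| Haemoglobin (g/dl) | In mg/dl | Multiple of the cut-off | Excluded? |
| --- | --- | --- | --- |
| 3 | 3,000 | 300 | no |
| 5 | 5,000 | 500 | no |
| 7 | 7,000 | 700 | no |
| 10 | 10,000 | 1,000 | no |
| 13 | 13,000 | 1,300 | no |
| 16 | 16,000 | 1,600 | no |
| 20 | 20,000 | 2,000 | no |

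The result does not depend on the assumed range, because any haemoglobin of 0.01 g/dl or more passes.

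**Step 3: size of the discrepancy.** The same digits read in g/dl would be 10 × 1,000 = 10,000 mg/dl, and 10,000 ÷ 10 = 1,000. This measures the gap between the two units. It does not establish which value the sponsor intended.

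**Step 4: look for a correction elsewhere.** No other part of the protocol gives a haemoglobin threshold. The Abstract has the words only, and the CBC row in the visit table carries no limit.

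**Step 5: rule out text extraction as the cause.** Where the extracted text is visibly damaged, characters are missing: the micro sign has gone from the bronchodilator dose and from the ELISA volumes. A lost character cannot explain item 5, where the prefix m would have had to be added. The glucose limit in item 1 makes a carried-over unit a plausible source, but that is a guess.

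**Step 6: check whether any statistical figure depends on it.** The sample-size statement uses a change from 456 to 482 metres in the study group, no improvement in the control group, power of 0.8 and 20% dropout, for 60 subjects. Haemoglobin is not among these inputs, nor does the stated analysis use it.

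**The case against.** The strongest reply is that this is a one-character slip that nobody would act on. Item 5 names the condition in words before it gives the number, and the Abstract repeats the exclusion. A limit of 0.01 g/dl is physically impossible, so a reader would probably see that the unit is wrong; a plausible but wrong number would do more harm. That stands, and it is why the point is minor. It does not remove the error, because the written threshold is still the one against which eligibility is judged.

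A reader might infer three stronger things that the protocol does not support.

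- **That anaemic patients do enter the trial.** The number would not stop them, but the verbal exclusion remains and nothing shows that the number was applied literally.
- **That the trial promises to exclude all anaemic patients.** Both places exclude only uncontrolled anaemia. Milder anaemia may be admitted on any reading.
- **That power falls by a stated amount.** Such a figure would need the share of enrolled patients affected, an assumption that they cannot respond to treatment, and the premise that the slip let them in. The protocol supplies none of these.

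Randomisation and blinding also mean that an eligibility slip does not by itself bias the comparison of arms. At most it could add variability or shift the enrolled population.

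**Conclusion.** Wrong as written, minor. The only numeric haemoglobin limit in the protocol equals 0.01 g/dl. No living patient falls below it, so the number does not implement the exclusion of uncontrolled anaemia that the Abstract states. The discrepancy is a factor of 1,000 if the digits are right and only the unit is wrong, which is for the sponsor to confirm.

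The conclusion rests on the unit conversion and on the absence of any other threshold in the protocol. The one outside assumption, a haemoglobin range of 3 to 20 g/dl, only illustrates the gap. No sample-size, power or analysis figure changes, and no bias between arms is claimed.

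**What to change.** The sponsor should confirm the intended haemoglobin value and its unit, and correct exclusion item 5 so that it carries out the exclusion of uncontrolled anaemia stated in the Abstract. Any screening form or eligibility check should then be compared with the corrected item. None is in the documents, so whether they carry the same unit is unknown. This review proposes no replacement threshold.

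The cost is one corrected line in the protocol and a check of the screening paperwork. Sample size, endpoints and analysis are unaffected.
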